#### Unsupervised learning for phenotype discovery

2.8.4

*Clustering analysis*: Data-driven identification of insomnia subtypes will utilize multiple clustering algorithms, including k-means, hierarchical clustering, and Gaussian mixture models. Clustering will be performed using standardized digital phenotyping features, and the optimal cluster number to be determined using silhouette analysis, gap statistics, and clinical interpretability.

*Dimensionality reduction*: Principal component analysis (PCA) and t-distributed stochastic neighbor embedding (t-SNE) will reduce data dimensionality while preserving important patterns. Uniform manifold approximation and projection (UMAP) will provide an additional visualization of high-dimensional relationships.

*Cluster validation*: Discovered clusters will be validated using internal measures (silhouette width and Dunn index) and external validation through clinical outcomes and biomarker profiles. Stability analysis using bootstrap resampling will assess cluster robustness across different sample compositions.

#### Supervised learning for prediction

2.8.5

*Model development*: Various machine learning algorithms will be employed for classification and regression tasks, including Random Forest, Extreme Gradient Boosting (XGBoost), Support Vector Machines, and neural networks. Tree-based models will be prioritized for their interpretability and robust performance using tabular healthcare data.

*Feature engineering*: Advanced feature engineering will create interaction terms, polynomial features, and domain-specific composite scores. Automated feature selection using recursive feature elimination and importance ranking will identify the optimal predictor sets.

*Model evaluation*: Predictive performance will be assessed using nested cross-validation to provide unbiased estimates. The classification tasks will use accuracy, sensitivity, specificity, area under the ROC curve (AUC), and precision-recall metrics. The regression tasks will employ mean absolute error, root mean square error, and R-squared values.

*Model interpretability*: Explainable AI techniques, particularly Shapley Additive explanation (SHAP) values, will quantify individual feature contributions to predictions. Partial dependence plots visualize feature effects, whereas permutation importance assesses global feature relevance.

#### Multimodal data integration

2.8.6

*Data fusion strategies*: Multiple fusion approaches will be implemented, including early fusion (feature concatenation), late fusion (prediction averaging), and intermediate fusion (learned representations). Ensemble methods combine the predictions from domain-specific models to leverage complementary information.

*Deep learning approaches*: Neural network architectures designed for multimodal data will include autoencoders for dimensionality reduction and transformer models for integrating sequential data. These approaches will be applied judiciously, with sample size considerations and interpretability requirements guiding the implementation.

#### Specialized analyses

2.8.7

*fNIRS data analysis*: Neuroimaging data analysis will follow established protocols using HOMER2/3 software. Statistical parametric mapping identifies task-related activation patterns, whereas functional connectivity analysis utilizes correlation and coherence measures. Group comparisons will be performed using general linear models with multiple comparison correction.

*Genomic data analysis*: Polygenic risk scores will be analyzed using linear models and population stratification controls. Gene expression data will employ differential expression analysis with multiple testing corrections. Pathway analysis using Gene Set Enrichment Analysis (GSEA) will identify biological mechanisms.

*Circadian analysis*: Cosinor analysis of physiological time series will employ nonlinear least-squares fitting to extract rhythm parameters. Population-mean cosinor analysis will test group-level rhythm differences, whereas individual cosinor analysis will characterize personal circadian profiles.

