#### Polygenic risk score calculation

2.7.3

Primary genomic analysis will focus on calculating insomnia-specific Polygenic Risk Scores (PRS) rather than novel gene discovery. The PRS calculation will utilize summary statistics from the most recent and largest genome-wide association study (GWAS) of insomnia, leveraging data from over 1.3 million individuals.

PRS computation will follow established protocols:

Quality control of genotype data including removal of variants with call rate <95%, minor allele frequency <1%, and Hardy-Weinberg equilibrium p-value <1×10^−6^Linkage disequilibrium clumping using European reference panels from the 1000 Genomes ProjectPRS calculation across multiple p-value thresholds (5×10^−8^, 0.001, 0.01, 0.05, 0.1, 0.5, and 1.0) to optimize predictive performance.Standardization of PRS values (mean=0, SD = 1) for interpretability

The resulting continuous PRS variable will quantify each participant’s genetic liability for insomnia, with higher scores indicating a greater genetic predisposition.

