#### Candidate gene expression analysis

2.7.4

Targeted gene expression analysis will be performed to examine the functional relevance of the key circadian and sleep-related genes. RNA will be extracted from buffy coat samples using the PAXgene Blood RNA Kit (PreAnalytiX, Switzerland), which preserved the *in vivo* gene expression profile at the time of blood collection.

Quantitative real-time PCR (qRT-PCR) will be performed using a focused panel of candidate genes.

*Core circadian clock genes*: *CLOCK, ARNTL/BMAL1, PER1, PER2, PER3, CRY1, CRY2, NPAS2*

*Clock-regulated genes*: *SIK1, SIK2, GSK3B (Glycogen Synthase Kinase 3 beta)*

*Neurotransmitter-related genes*: *COMT (Catechol-O-Methyltransferase)*

Gene expression levels will be normalized to housekeeping genes (*GAPDH* and *ACTB*) and will be expressed as fold-changes relative to a pooled reference sample.

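### GSEA cannot identify biological mechanisms from a pre-selected panel of 12 qRT-PCR genes, the only gene-level data the article describes for it

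*Protocol article*

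**What the plan says.** Under its genomic heading, section 2.8.7 (Specialized analyses) first covers the polygenic risk scores, then states "Gene expression data will employ differential expression analysis with multiple testing corrections", and continues directly with "Pathway analysis using Gene Set Enrichment Analysis (GSEA) will identify biological mechanisms".

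The expression data are defined in section 2.7.4 (Candidate gene expression analysis): "Targeted gene expression analysis will be performed to examine the functional relevance of the key circadian and sleep-related genes", and "Quantitative real-time PCR (qRT-PCR) will be performed using a focused panel of candidate genes". Three groups are listed:

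- core clock genes: "CLOCK, ARNTL/BMAL1, PER1, PER2, PER3, CRY1, CRY2, NPAS2" (8 genes);
- clock-regulated genes: SIK1, SIK2 and GSK3B (3 genes);
- neurotransmitter-related: COMT (1 gene).

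GAPDH and ACTB serve only for normalization.

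The genome-wide array has a different use. Section 2.7.3 (Polygenic risk score calculation) says: "Primary genomic analysis will focus on calculating insomnia-specific Polygenic Risk Scores (PRS) rather than novel gene discovery". The limitations in the Discussion likewise describe the genomic work as mainly polygenic scores and candidate gene expression.

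**The concern.** GSEA is a competitive method. It ranks all measured genes by their association with group and asks whether the members of a set gather at one end of that ranking more than the remaining genes do. It needs a broad ranking with many genes outside each set. The described assay supplies 12 genes, picked because they were already thought relevant to circadian rhythm and sleep.

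Three consequences follow. No pathway without a gene on the panel can be found. A pathway that is flagged reflects in part which genes were put on the panel. A shift shared by the whole panel leaves nothing to contrast, so it is largely invisible to the method.

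What is at stake is the interpretation of the expression results. A pathway result would be presented as a mechanism found in the data, when the choice of assay had settled beforehand which pathways could appear. A real change across the panel could also be reported as no enrichment.

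**Working it through.** The article gives no sample size, power or error rate for GSEA or for gene expression, so there is no stated figure to reproduce for this analysis. As background, the general power statement in section 2.9 does reproduce: 240 versus 80 at d = 0.36 and two-sided alpha 0.05 gives 79.6%, against the stated figure of about 80%.

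**Step 1: panel count (section 2.7.4).** 8 + 3 + 1 = 12 genes. Core clock: 8/12 = 67%. Clock or clock-regulated: 11/12 = 92%. Background for the core-clock set: 12 − 8 = 4 genes, of which 3 are clock-regulated.

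**Step 2: is there another ranking?** The polygenic score is one number per participant, not a statistic per gene. The article describes no gene-level association analysis of the array data. The 12 expression genes are the only gene-level list it provides.

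**Step 3: how coarse the gene ranking is (illustration only).** Take the three panel headings as the gene sets and permute gene labels. The smallest attainable p-value for a set of k genes is then 1/C(12, k):

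- core clock, k = 8: 1/495 = 0.002;
- clock-regulated, k = 3: 1/220 = 0.0045;
- neurotransmitter-related, k = 1: 1/12 = 0.083.

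A set that holds all 12 genes has p = 1. The article states neither the permutation scheme nor the gene sets.

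**Step 4: behaviour of GSEA on this panel.** A simulation of 3,000 runs per scenario used the enrolled 249 and 89 participants (section 2.9), the weighted enrichment score for the core-clock set and all 495 gene-label assignments, with p ≤ 0.05 counted as flagged in either direction. A between-gene correlation of 0.3 was assumed. The shift is d = 0.36, borrowed from section 2.9. The standard error of d is √(1/89 + 1/249) = 0.1235, so a shifted gene has expected z = 0.36/0.1235 = 2.91 and single-gene power of about 83%.

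| Genes shifted by d = 0.36 | Core-clock set flagged |
|---|---|
| none | 4.1% |
| all 12 | 3.7% |
| 8 core clock only | 98% |
| 4 others only | 91% |

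The second row shows that a shift of the whole panel goes undetected, although each gene on its own would be detected about 83% of the time. The last row shows the core-clock set flagged when none of its genes has changed. The four other genes move up the ranking and push the core genes to the opposite end. With a background of four genes, the result depends on which genes happen to be the comparators.

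**The case against.** **The input is inferred.** Section 2.8.7 does not say which data feed GSEA, its heading also covers the genotypes, and section 2.7.2 describes an array of over 600,000 variants. Section 2.7.3 limits the primary genomic focus and does not forbid every gene-level analysis. This caveat stands. The expression reading is still the likelier one: the GSEA sentence directly follows the expression sentence, and no gene-level genotype analysis is described. If another input is meant, it needs to be named.

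**Stronger readings do not hold.** A reader might infer that a circadian finding would be reported whatever the data show, because the panel is enriched for clock genes by construction. That describes over-representation testing of a gene list against a genome background. The article names GSEA, and within the panel the simulated null rate was 4.1%, close to nominal. A reader might also infer that the neurotransmitter category can never reach 0.05. That holds only under gene-label permutation with the single gene COMT treated as a set. Permuting participants removes the floor, but leaves the list at 12 genes.

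**Detail may sit elsewhere.** A condensed article may leave permutation schemes, gene sets and model covariates to a fuller document. For that reason the absence of a blood-draw-time term from the expression models is not raised here. The same defence does not rescue GSEA. The article itself fixes the gene list, the method and the claim, and a further document cannot supply a background that the described assay does not measure.

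**Impact is limited.** This is one exploratory analysis. The group comparisons, clustering, polygenic scores and single-gene expression tests are untouched. That is right, and it bears on the priority of the point, not on its correctness.

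**Conclusion.** The point holds: on the data described, the stated method cannot support the stated conclusion. The panel count is exact: 12 genes, 8 of them core clock, with a background of 4. It follows without further assumption that no pathway lacking a panel gene can be found and that any result is confined to the panel.

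The size of the distortion (3.7% flagged for a panel-wide shift, 91% when only the other four genes shift) rests on assumptions: gene-label permutation, the core-clock heading taken as the gene set, correlation 0.3 and d = 0.36. These figures are illustrations, as are the p-value floors. The conclusion also assumes that the expression panel is the input to GSEA, as the order of sentences indicates. The consequence is one of interpretation for a secondary, exploratory analysis. It should be corrected, but it does not threaten the main comparisons.

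**What to change.** 1. In section 2.8.7, delete GSEA and the claim that it will identify mechanisms. If a genome-wide gene-level input is meant, name it and say how the gene-level statistics will be obtained.
2. Test the 12 genes individually. Section 2.8.7 already promises a multiplicity correction; state that it is the Benjamini-Hochberg procedure of section 2.8.2, with the 12 genes as one family.
3. Add a self-contained global test for each of the two multi-gene families (8 core clock, 3 clock-regulated). For example, sum the squared test statistics over the family and refer the sum to its distribution under permutation of participant group labels. This asks whether any gene in the family differs between groups, so it can detect a shift common to all of them, and it needs no background genes. COMT stays a single-gene test.
4. Limit the conclusions to differences between insomnia and control groups in the named genes, described as candidate-gene results.

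The cost is a few sentences of analysis text and two permutation tests. No new assay or data are needed. Sections 2.7.4 and 2.8.7 describe the expression assays and their analysis in the future tense, so on the article's own account the change can be made before results are seen.

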#### Data processing and feature generation

2.5.3

The raw digital data from the wearable devices and the SOMDAY smartphone application undergo a rigorous processing pipeline to generate a comprehensive set of digital phenotypes. This approach is not limited to a single analytical plan, and the processed data can be used for various advanced statistical and computational analyses, such as machine learning, to explore the complex relationships between different data modalities and identify meaningful patterns. The processing strategies for each data modality are meticulously designed to provide a rich dataset for subsequent analyses aimed at elucidating biopsychosocial phenotypes of sleep.

The periodic nature of sleep and activity is the key focus of our analysis. Raw data from wearable devices, including continuous heart rate and step counts, will be processed to extract a range of clinically relevant features. For continuous variables such as heart rate and step counts, cosinor analysis (58, 59) will be performed to characterize circadian rhythms. This will involve processing the data within 72-hour intervals to derive key circadian rhythm parameters, including midline estimating statistic of rhythm (MESOR), amplitude, and acrophase. MESOR represents the rhythm-adjusted mean and provides a robust measure of the average parameter level over time. Amplitude quantifies the extent of predictable variation within the circadian cycle, reflecting the strength of the rhythm. The acrophase indicates the timing of the peak value, which offers insight into circadian alignment or misalignment.

In addition, a range of other activity-related metrics will be calculated to provide a more detailed view of daily patterns. These will include the least active 5-hour period (L5), the most active 10-hour period (M10), interdaily stability (IS), and intradaily variability (IV) (60). L5 and M10 will be calculated using the moving average method to identify minimum and maximum activity periods, respectively. IS quantifies the day-to-day regularity of a rhythm, whereas IV measures rhythm fragmentation within a day. These features will be segregated by weekdays and weekends to capture distinct lifestyle patterns.

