The raw, continuous heart rate data collected at 5-minute intervals will be a critical component for understanding circadian rhythmicity and autonomic function. We will apply cosinor analysis to these data, similar to the method used for step counts, to extract key rhythm parameters. Specifically, we will derive the MESOR, amplitude, and acrophase of the heart rate rhythm over a 72-hour window. The MESOR of the heart rate rhythm reflects the average heart rate, whereas the amplitude provides a measure of the magnitude of diurnal heart rate fluctuation, which can be an indicator of autonomic nervous system activity. The acrophase of the heart rate rhythm indicates the time of day when the heart rate is at its peak and is a key metric for assessing the phase of the circadian clock. These features will also be calculated separately for weekdays and weekends to account for differences in daily routines and their impact on physiological rhythms. Additionally, heart rate data collected during sleep will be used to derive the resting heart rate (RHR) as a proxy for autonomic nervous system activity, a measure known to be associated with arousal and stress. Heart rate data collected every 5 minutes from the Fitbit Inspire 3 were used to evaluate circadian rhythmicity and autonomic function. Because the device provides pulse rate variability derived from photoplethysmography(PPG) rather than true ECG based HRV, short term beat to beat analyses were not performed. Instead, resting heart rate during sleep and cosinor rhythm parameters were used to indirectly assess long term autonomic patterns. This approach allows for the characterization of autonomic rhythms in real world conditions.

Self-reported data collected via the SOMDAY application will undergo specific processing to reflect the differential impact of behavior on circadian regulation. A time-of-day weighted scoring system will be applied to substances such as alcohol and caffeine, based on their intake time (morning, afternoon, or night). For example, the disruptive potential of caffeine on sleep will be weighted more heavily for intake closer to bedtime. Similarly, stress levels and nap durations will be processed with weights to reflect their influence on circadian rhythms, a key focus of this study.

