#### Group comparison analyses

2.8.2

*Primary group comparisons*: Between-group differences (insomnia vs. controls) will be assessed using appropriate statistical tests based on the data distribution and measurement level. Independent samples t-tests (or Mann-Whitney U tests for non-normal distributions) will be used to compare continuous variables. Chi-square tests will evaluate categorical variables.

*Secondary analyses*: Subgroup comparisons will examine differences based on sleep disorder risk (e.g., RLS symptoms, sleep apnea risk) and demographic factors. Analysis of covariance (ANCOVA) will control for potential confounders, including age, sex, and comorbid conditions.

*Multiple comparisons*: Given the large number of variables, false discovery rate (FDR) correction using the Benjamini-Hochberg procedure will be applied to control for multiple testing. Both uncorrected and FDR-corrected p-values will be reported to balance the discovery and rigor.

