### Sample size and power considerations

2.9

Participant recruitment for this deep phenotyping study has been completed in accordance with the original protocol design. The study employed a rolling, observational recruitment framework, with the goal of achieving a sample size sufficient for robust multimodal analyses across clinical, behavioral, physiological, and digital domains. Based on feasibility and methodological considerations, the protocol specified minimum recruitment targets of approximately 330 participants in total, including at least 240 individuals with insomnia and at least 80 good-sleeper controls.

These targets were established to ensure statistical adequacy for the key analytic aims while maintaining the feasibility of comprehensive multimodal data collection. Power estimations at the design stage indicated that, under this allocation (unequal groups, α = 0.05), the study would achieve about 80% power to detect standardized mean differences of Cohen’s d ≈ 0.36, which represents a small-to-moderate and clinically meaningful effect commonly observed in sleep research. For correlational analyses involving continuous variables, a total sample of this magnitude provides approximately 80% power to detect correlations of r ≈ 0.15–0.16, assuming complete data pairs. For predictive analyses, a balanced-class equivalent sample of this scale would permit area under the curve (AUC) estimates around 0.70 with a standard error of approximately 0.03, corresponding to a 95% confidence interval of roughly ±0.06. These calculations reflect the expected precision and effect sizes typical of multimodal insomnia research rather than formal hypothesis testing for a single endpoint.

In practice, 338 participants were enrolled, comprising 249 individuals with insomnia and 89 good-sleeper controls, consistent with the predefined recruitment objectives. Within the insomnia group, severity distribution according to the Insomnia Severity Index (ISI) was mild = 130, moderate = 101, severe = 18. Analyses involving ISI will therefore treat severity as a continuous variable or use pooled strata where appropriate, given limited sample sizes in the extreme categories. The analytic plan includes standard measures to ensure that statistical modeling remains commensurate with the available data, including internal cross-validation and regularization to reduce overfitting in multivariate and machine-learning models.

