## Discussion

3

This protocol presents a comprehensive and multimodal approach to the deep phenotyping of insomnia, a condition widely recognized for its clinical and etiological heterogeneity. Conventional assessment methods, often relying on demographic data analysis (61), self-reported subjective reports (62, 63), or single-night objective metrics, have shown limited reliability and poor concordance with perceived sleep quality (64, 65). Demographic data analyses and self-reported assessments (61–63) make it difficult to capture the complexity of insomnia. Therefore, our study aims to overcome these limitations by integrating data from clinical questionnaires, continuous digital phenotyping, functional neuroimaging, and genomics to comprehensively characterize the individual experiences of insomnia.

The primary strength and novelty of this protocol are its methodological integration. By combining continuous real-world data from wearables and smartphones with laboratory neurophysiological and biological measures, we can create a dataset of unprecedented depth and breadth. This approach intentionally bridges the gap between subjective, symptom-focused, and objective sleep measurement studies. Compared to single-night laboratory polysomnography, our wearable-based monitoring provides less detail on sleep architecture but offers far greater ecological validity by sampling multiple nights in the participant’s natural environment. This design enables the capture of the dynamic and fluctuating nature of insomnia, which static, single-time-point assessments often fail to do. However, this approach is not without its limitations. The sheer volume and complexity of multimodal data require sophisticated analytical techniques and careful management to avoid false discoveries. The intensive protocol may also impose a burden on participants, and the single-center design may limit the generalizability of the findings.

Implications of this deep phenotyping approach in sleep medicine are substantial. The primary object is to support a paradigm shift from undifferentiated care to personalized management. Tailoring insomnia treatments, such as cognitive behavioral therapy for insomnia (CBT-I) or pharmacotherapy, requires recognizing biologically distinct subtypes, including those characterized by physiological hyperarousal or circadian rhythm disruption (66–68).

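### The group test of circadian rhythm uses the population-mean cosinor, whose amplitude mixes individual rhythm strength with how closely participants' peak times agree

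*Protocol article*

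**What the plan says.** Section 2.8.7 (Specialized analyses) gives the two forms of cosinor analysis different jobs: "Population-mean cosinor analysis will test group-level rhythm differences, whereas individual cosinor analysis will characterize personal circadian profiles". The inferential role goes to the population-mean method and the descriptive role to the individual fits.

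Section 2.5.3 (Data processing and feature generation) says what the parameters mean. On amplitude in general: "Amplitude quantifies the extent of predictable variation within the circadian cycle, reflecting the strength of the rhythm". On heart rate: "the amplitude provides a measure of the magnitude of diurnal heart rate fluctuation, which can be an indicator of autonomic nervous system activity". Timing is kept as a separate quantity: "The acrophase indicates the timing of the peak value, which offers insight into circadian alignment or misalignment". The parameters are fitted to short stretches of data: "Specifically, we will derive the MESOR, amplitude, and acrophase of the heart rate rhythm over a 72-hour window". Step counts are handled the same way.

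Section 2.8.2 (Group comparison analyses) has a general rule that does not mention cosinor parameters: "Independent samples t-tests (or Mann-Whitney U tests for non-normal distributions) will be used to compare continuous variables".

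Section 2.9 gives the sample: "338 participants were enrolled, comprising 249 individuals with insomnia and 89 good-sleeper controls".

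**The concern.** A population-mean cosinor averages each person's cosine and sine coefficients and takes the length of the mean vector as the group amplitude. People whose peaks fall at different times partly cancel each other. The group amplitude therefore depends on two things: how strong each person's rhythm is, and how well the peaks line up across people. Comparing it between cohorts tests the product of the two. That equals a test of rhythm strength only when both cohorts have the same phase spread.

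Section 2.5.3 treats strength and timing as separate, and reads amplitude as strength. A lower population-mean amplitude in one cohort could therefore be taken for a blunted rhythm or an autonomic change when only the peak times are more scattered. A true difference in individual amplitude could equally be cancelled or turned round. This bears on the first objective in section 2.8, describing how the insomnia and control groups differ, for both heart rate and step counts.

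**Working it through.** **Inputs.** From the article: 249 and 89 participants (section 2.9), α = 0.05 (section 2.8.8, taken as two-sided), and the design effect d ≈ 0.36 (section 2.9). Assumed, because the article gives none: between-person acrophase SDs of 1.0 to 3.0 h, amplitude CV of 30-40%, the same mean acrophase in both cohorts, and phase roughly normal and independent of amplitude.

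**The plan's own figure.** Section 2.9 states about 80% power for d ≈ 0.36. A two-sided t-test at 240 versus 80 gives 79.6%, so the figure reproduces. At the enrolled 249 versus 89 it is 83.0%. No power figure is given for the cosinor test.

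**Formula.** With individual amplitude A and phase φ, each person contributes β = A cos φ and γ = A sin φ. The population-mean amplitude is √(mean(β)² + mean(γ)²) ≈ mean(A) × exp(-s²/2), with s = 2π × SD/24.

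| Acrophase SD | s (radians) | exp(-s²/2) |
|---|---|---|
| 1.0 h | 0.262 | 0.966 |
| 1.5 h | 0.393 | 0.926 |
| 2.0 h | 0.524 | 0.872 |
| 2.5 h | 0.654 | 0.807 |

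With equal individual amplitudes, the apparent deficit in the wider cohort is:
- 1.5 versus 1.0 h: 1 - 0.926/0.966 = 4%
- 2.0 versus 1.5 h: 1 - 0.872/0.926 = 6%
- 2.0 versus 1.0 h: 1 - 0.872/0.966 = 10%
- 2.5 versus 1.5 h: 1 - 0.807/0.926 = 13%

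**Simulated rejection rates.** These use 249 versus 89, identical individual amplitude distributions and nominal 5%. The first SD is for insomnia. Ranges cover pooled and separate variances, with and without modest estimation noise on the coefficients.

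| Phase SD | Population-mean amplitude, CV 30% | Population-mean amplitude, CV 40% | Welch on individual amplitudes |
|---|---|---|---|
| 1.5 vs 1.5 h | 4-6% | about 5% | 4-6% |
| 1.5 vs 1.0 h | 18-20% | about 14% | 4-6% |
| 2.0 vs 1.5 h | 26-31% | 17-21% | 4-6% |
| 2.0 vs 1.0 h | 64-74% | about 50% | 4-6% |
| 2.5 vs 1.5 h | 79-87% | 60-68% | 4-6% |
| 3.0 vs 2.0 h | 83-90% | 68-77% | 4-6% |

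The direction follows whichever cohort is more scattered. With the controls wider (1.5 versus 2.0 h, CV 30%), the test rejects about 27% of the time, as a higher amplitude in insomnia.

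**Masking and reversal.** Suppose individual amplitude is truly higher in insomnia by d = 0.36 at CV 30%. The mean is then 0.36 × 0.30 = 10.8% higher.
- At 2.0 versus 1.0 h, the population-mean ratio is 1.108 × 0.872/0.966 = 1.00. The difference vanishes, and the test rejects about 5% of the time.
- At 2.5 versus 1.5 h, it is 1.108 × 0.807/0.926 = 0.97. The sign is reversed; the test rejects 8-13% of the time, nearly always in the wrong direction.
- A Welch test on individual amplitudes has about 80% power in both cases.

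**The case against.** **The stated target is the group rhythm, not individual amplitude.** A cohort with less aligned peaks does have a different group rhythm, so rejection is not an error for that target. This is fair as far as it goes. But amplitude is the only measure of strength that the article interprets, and it interprets it as a property of the rhythm with timing held apart. Nothing warns that the population-mean version means something else.

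**Section 2.8.2 already allows t-tests on individual amplitudes, and section 2.8.7 does not withdraw them.** True, and running them would expose the artefact. But section 2.8.2 does not name cosinor parameters, and section 2.8.7 names another method for rhythm differences. If the two disagreed, no rule says which stands.

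**Unequal spread is not shown.** This objection stands. A reader might infer that insomnia will have the wider spread and will therefore be reported as having a weaker rhythm. The article does not support that. Section 2.2 excludes shift work and irregular schedules from both cohorts, and does not select controls for uniform timing. The Discussion mentions subtypes, "including those characterized by physiological hyperarousal or circadian rhythm disruption", but when arguing for tailored treatment, not when describing this sample's phases. Nor does the article say how a population-mean result will be worded.

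**Multiplicity control.** The rates above are at an unadjusted 5%. The false discovery rate procedure in section 2.8.2 would lower them but leaves the bias in place, and uncorrected p-values are also to be reported.

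**Individual amplitudes are not immune.** This also stands. Phase shifts from day to day within a 72-hour window shrink the fitted amplitude too. For three equally weighted days with day-to-day phase SD s, the loss is about (s²/2)(1 - 1/3) = s²/3. That is 0.154/3 = 5.1% at 1.5 h and 0.069/3 = 2.3% at 1.0 h, against 7.4% and 3.4% for the same between-person spread. In one check with unequal within-window shifts, Welch rejected 15% of the time.

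**Conclusion.** The point holds conditionally. The population-mean amplitude does not isolate rhythm strength, and its comparison is valid for that purpose only if the cohorts have equal phase spread. With equal spread the test keeps about 5%. Under assumed values, a 0.5 h gap in acrophase SD gives about 14-30% false rejection at CV 30-40%, and a 1 h gap about 50-90%. The article supplies no phase SD or amplitude CV, so neither the size nor the direction in this sample can be known from it. MESOR comparisons are unaffected. This is a better choice of test that costs little; it is not evidence that the rhythm results will be wrong.

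**What to change.** In section 2.8.7:
- Make the group test of rhythm strength a comparison of per-participant cosinor amplitude, by Welch t-test or by a linear model with the covariates planned in section 2.8.2.
- Compare acrophase location, and separately its between-person dispersion, with circular methods, each as a named result.
- Keep the population-mean cosinor as a descriptive group curve, and state that its amplitude combines rhythm strength with phase alignment.

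The per-participant parameters are already to be derived under section 2.5.3, so no new data are needed. The cost is that group rhythm results become several quantities instead of one test. Individual amplitudes remain sensitive to day-to-day phase shifts within the 72-hour window, which should be stated when they are interpreted.
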